## Data Analysis

The hypothesis that increased saturated fat derived primarily from dairy products will increase levels of large HDL2 and large LDL in pattern B individuals, with no significant effect on small, dense LDL, will be tested by comparing the mean change in large LDL levels as measured by ion mobility. The statistical significance will be evaluated by one-way analysis of variance with the factor being high or low saturated fat intake. Similar analyses will be used to test the effects of saturated fat on HDL cholesterol, and LDL diameter. Comparison of LDL pattern conversion rate between high and low saturated fat diets will be analyzed by Chi-squared analysis.

**Table 1** shows the detectable and expected differences using data from the high fat/low fat study described above [27]. Expected differences are derived from correlations of the change in fatty acid intake (assessed by food records of prescribed diets) and change in LDL measurements. The correlations were used to select the differences in SFA (12%), myristic (2.5%), and palmitic acid (5.5%) levels needed for a detectable effect in the primary endpoints given 25 subjects per group. These are approximately equal to the mean change in intake in our previous study. With 25 subjects/group, we have adequate power (80%) to detect the expected changes in LDL I, LDL diameter, and HDL2b given either a 12% difference in saturated fat or a 2.5% difference in myristic acid between the two diets. Although the lipoprotein subfraction predictions are based on measurements made by analytical ultracentrifugation or gradient gel electrophoresis, we expect the ion mobility method to be equally or more

precise. Typical standard deviations for measurements by ion mobility are 20.9 mg/dl for large LDL and 3.5 Å for LDL diameter. In addition, we will use the average value of measurements from two blood draws on consecutive days to reduce variance and increase power.

**Table 1:** Detectable (80% power) and expected difference for primary endpoints

|               | SD of difference | Detectable differences between groups  |            | Expected Difference w/ 12% ΔSFA | Expected Difference w/ 2.5% Δ14:0 |
|---------------|------------------|----------------------------------------------------|------------|---------------------------------|-----------------------------------|

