|               |                  | Difference                                         | % baseline |                                 |                                   |
| HDL2b (mg/dl) | 11.5             | 6.5                                                | 25         | 7.9 mg/dl                       | 10.7 mg/dl                        |
| LDL-I (mg/dl) | 29.6             | 16.6                                               | 22         | 39.2 mg/dl                      | 49.6 mg/dl                        |
| LDL diam (Å)  | 5.0              | 2.9                                                | 1.7        | 4.9 Å                           | 6.1 Å                             |

Detectable differences assume the average of 2 baseline and 2 post-diet measurements

To estimate predicted LDL pattern conversion rates, we used logistic regression to achieve a best approximation of the expected conversion rate between the two diets. At 35% carbohydrate intake and 12% difference in saturated fat, we expect that 48% pattern B participants will convert to pattern A. With a 2.5% difference in myristic acid, we predict a 71% conversion rate. Similar power estimates were obtained with a 5.5% difference in palmitic acid.

Other endpoints will include plasma triglyceride, total cholesterol, LDL-cholesterol, HDL cholesterol, apoB, apoAI, and LDLII-IV. **Table 2** presents the detectable differences in these endpoints estimated at 80% statistical power, 5% significance using baseline concentrations and standard deviation of response observed in our previous controlled dietary trials. Detectable differences are in accordance with power estimates from previous diet studies.

Sample size estimation is determined by lipoprotein endpoints, as not enough data is available to estimate expected differences in CETP, HL, and LPL activity levels. Based on previous data, we have adequate power (86%) to detect a difference of 15% baseline levels of HL activity between groups and reasonable power (52%) to detect a difference of 30% baseline levels of LPL between groups.

**Table 2.** Detectable differences (80% power) in other plasma lipid and lipoprotein levels

|                            | Baseline concentrations | Standard deviation of difference | Differences between groups         |            |
|----------------------------|-------------------------|----------------------------------|------------------------------------|------------|

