|                            |                         |                                  | Detectable Difference  | % baseline |
| Triglycerides (mg/dL)      | 215.31±106.34           | 117.97                           | 65.98                              | 30.65      |
| Total cholesterol (mg/dL)  | 206.79±32.53            | 25.97                            | 14.52                              | 7.02       |
| LDL-chol(mg/dL)            | 127.55±30.19            | 24.60                            | 13.76                              | 10.79      |
| HDL-C(mg/dl)               | 36.49±6.05              | 5.34                             | 3.05                               | 8.36       |
| Apo AI (mg/dL)             | 109.21±14.17            | 9.49                             | 5.31                               | 4.87       |
| Apo B (mg/dL)              | 99.78±18.03             | 25.50                            | 14.26                              | 14.29      |
| LDL-2 (mg/dL)  | 90.03±38.62             | 35.00                            | 19.58                              | 21.75      |
| LDL-3 (mg/dL)  | 91.33±28.76             | 25.02                            | 13.99                              | 15.31      |
| LDL-4 (mg/dL)  | 18.72±14.39             | 15.71                            | 8.78                               | 46.92      |

Detectable differences assume the average of 2 baseline and 2 post-diet measurements

LDL subfraction data for this table was derived from a more recent study than data shown in Table 1, but show very similar % baseline differences.

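### One-way ANOVA on change subtracts the run-in value but does not adjust for it; ANCOVA on the run-in mean would be more precise for one degree of freedom

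*Protocol*

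**What the plan says.** The Data Analysis section states both the outcome and the test. The main hypothesis "will be tested by comparing the mean change in large LDL levels as measured by ion mobility", and "The statistical significance will be evaluated by one-way analysis of variance with the factor being high or low saturated fat intake". Similar analyses are planned for HDL cholesterol and LDL diameter. No covariate is named.

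The run-in value does enter the analysis, as the baseline from which change is taken. Two draws are averaged at each time point, and both tables carry the footnote "Detectable differences assume the average of 2 baseline and 2 post-diet measurements". Under Clinic Visits, the stated purpose of the second run-in draw (V2b) is more statistical power.

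On size, the section claims: "With 25 subjects/group, we have adequate power (80%) to detect the expected changes in LDL I, LDL diameter, and HDL2b". Table 1 gives an SD of difference for these three primary endpoints but no baseline SD. Table 2 covers the other endpoints, including LDL-2 to LDL-4, and gives both a baseline SD and an SD of difference. Its detectable differences are "estimated at 80% statistical power, 5% significance using baseline concentrations and standard deviation of response".

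**The concern.** A change score fixes the coefficient of the run-in value at 1. If the true regression of the post-diet value on the run-in value is flatter, subtraction over-corrects: run-in noise is carried into the change, and a chance difference in run-in means between the arms moves the estimated diet effect in the opposite direction. ANCOVA estimates the slope from the data and removes both effects. At stake are precision in a trial of 50 completers and an estimate that partly reflects which arm happened to start higher. The covariate is already collected, in duplicate, for every participant who reaches randomisation.

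**Working it through.** **1. Reproduce the plan's detectable differences.** Inputs: 25 per arm, 80% power, 5% significance (taken as two-sided), multiplier 1.96 + 0.84 = 2.80. The tables reproduce when the listed SD of difference is divided by √2, in line with the averaging footnote: δ = 2.80 × (SDd/√2) × √(2/25).

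- HDL2b (SDd 11.5): 6.44, stated 6.5
- LDL-I (29.6): 16.59, stated 16.6
- LDL diameter (5.0): 2.80, or 2.86 with the t distribution; stated 2.9
- LDL-2 (35.00): 19.61, stated 19.58
- LDL-3 (25.02): 14.02, stated 13.99
- LDL-4 (15.71): 8.80, stated 8.78

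**2. Correlation implied by Table 2.** The rows give baseline SD and SD of difference, for example "90.03±38.62 | 35.00" for LDL-2 and "91.33±28.76 | 25.02" for LDL-3. Assume the same SD before and after diet. Then ρ = 1 − SDd²/(2·SDb²).

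- LDL-2: 1 − 1225.0/(2 × 1491.5) = 0.59
- LDL-3: 1 − 626.0/(2 × 827.1) = 0.62
- LDL-4: 1 − 246.8/(2 × 207.1) = 0.40

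**3. Variance cut with the listed SDs.** Residual variance is 2·SDb²(1−ρ) for change and SDb²(1−ρ²) for ANCOVA, so the cut is (1−ρ)/2 = SDd²/(4·SDb²).

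**4. Variance cut with two-draw averaging.** If averaging halves the variance of change, all of that variance is treated as independent draw-to-draw error. The variance of change becomes SDd²/2 and the baseline variance SDb² − SDd²/4. For LDL-2: 1491.5 − 306.25 = 1185.3; ρ = 1 − 612.5/(2 × 1185.3) = 0.74; cut 12.9%.

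| Endpoint | SDb | SDd | Cut, listed SDs | Cut, averaged |
|---|---|---|---|---|
| LDL-2 | 38.62 | 35.00 | 20.5% | 12.9% |
| LDL-3 | 28.76 | 25.02 | 18.9% | 11.7% |
| LDL-4 | 14.39 | 15.71 | 29.8% | 21.2% |
| HDL-C | 6.05 | 5.34 | 19.5% | 12.1% |
| Triglycerides | 106.34 | 117.97 | 30.8% | 22.2% |
| Total cholesterol | 32.53 | 25.97 | 15.9% | 9.5% |
| LDL-C | 30.19 | 24.60 | 16.6% | 10.0% |
| Apo AI | 14.17 | 9.49 | 11.2% | 6.3% |

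Apo B is left out. Its SD of difference, 25.50, equals 18.03 × √2, so the implied correlation of exactly zero may not be an observed value.

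The stated detectable differences already include averaging, so the matching improvement is stated value × √(1 − averaged cut): LDL-2 19.58 to 18.27, LDL-3 13.99 to 13.15, LDL-4 8.78 to 7.79 mg/dL.

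**5. Cost of estimating the slope.** With 50 participants, the variance of the effect is inflated by about 1/(50 − 4) = 2.2%. A simulation of 20,000 trials with 25 per arm, using the listed SDs, gave net cuts of 18%, 17% and 28% for LDL-2, LDL-3 and LDL-4.

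**6. Sensitivity to equal SDs.** Let the post-diet SD be k·SDb. Then ρ = (1 + k² − SDd²/SDb²)/(2k), and the cut is 1 − k²·SDb²(1−ρ²)/SDd². With the listed SDs:

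- k = 0.8: 42% (LDL-2), 41% (LDL-3), 50% (LDL-4)
- k = 1.2: 4%, 3%, 12%

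**7. Chance imbalance.** A run-in difference of one standard error, SDb·√(2/25), shifts the change-score estimate by (1−ρ) times that amount. On the averaged basis the shifts are 2.52, 1.71 and 1.45 mg/dL for LDL-2 to LDL-4, or 13%, 12% and 17% of the stated detectable differences.

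**The case against.** The strongest reply is that nothing is broken. Under randomisation, a comparison of mean change is valid and unbiased, the run-in data are used by subtraction, and two draws are averaged. A SAP that is not at hand could add the covariate. All of that stands, and it makes this a matter of efficiency. It does not make the change score as efficient as ANCOVA, and the protocol states a specific unadjusted test, so this is not a blank left to a SAP.

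The second reply is that the quantified gain concerns endpoints the protocol calls other. This also stands. A reader might fill the gap by pairing the ion-mobility SDs in the text (20.9 mg/dl and 3.5 Å) with Table 1's SDs of difference (29.6 and 5.0), which would suggest a cut of about 50% for large LDL and LDL diameter. The documents do not support this: Table 1 rests on other measurement methods, and the text does not say whether the ion-mobility figures are between-person SDs or SDs of change.

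A reader might also infer that the main comparison is underpowered without ANCOVA. For large LDL it is not. At the expected 39.2 mg/dl and the full SD of 29.6, 39.2/(29.6 × √0.08) = 4.68, which is power above 99%. For HDL2b, on the protocol's averaged basis, 7.9/(8.13 × √0.08) = 3.43, or about 93%.

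Finally, a reader might think that enrolling only pattern B participants biases the change scores through regression to the mean. Selection takes place at screening, while the analysis baseline is V2, after a three-week run-in, and any regression from selection affects both arms alike in expectation. Only ordinary chance imbalance at V2 remains.

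**Conclusion.** The point holds as an available gain in efficiency. The planned one-way ANOVA on change is sound but leaves precision unused. For LDL-2 to LDL-4, baseline adjustment would lower residual variance by about 19-30% with the listed SDs, or 12-21% if averaging halves the variance of change. Under equal SDs these two sets bracket the gain, because averaging draws taken days apart cannot remove true differences between people in response to diet.

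The figures rest on two assumptions: equal SDs before and after diet, and baseline SDs and SDs of difference that belong to the same population. The second is not confirmed, since Table 2 is described as "using baseline concentrations and standard deviation of response observed in our previous controlled dietary trials", with more than one trial as its source. With a post-diet SD 1.2 times baseline, the listed-SD gain falls to 3-12%. For LDL-I, HDL2b and LDL diameter the direction is expected to be the same, but the size cannot be computed from the protocol.

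**What to change.** In the Data Analysis section, replace the one-way ANOVA on change with a prespecified ANCOVA. The outcome is the mean of V3a and V3b, the factor is diet arm, and the covariate is the mean of V2a and V2b for the same variable. Using change as the outcome with the same covariate gives an identical diet effect, so the hypothesis can still be worded in terms of change. Apply the model to large LDL, the HDL measures and LDL diameter, and keep the unadjusted comparison of change as a sensitivity analysis. If a SAP already specifies adjustment, bring the protocol text into line with it.

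The cost is a change of wording, one degree of freedom and about 2% variance inflation, with no new data. Sex is an optional further covariate at one more degree of freedom. The covariate should be fixed before outcome data are seen, since one chosen afterwards would carry less weight.

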## 2. Research Project Objectives and Hypothesis

Our overall objective is to investigate the role of dairy fat in modulating lipoprotein profiles associated with cardiovascular disease (CVD) risk. In this study, we will test the following specific hypotheses regarding changes in plasma lipoproteins induced by a diet high in myristic acid and other saturated fats derived primarily from dairy sources in individuals with LDL subclass pattern B (a trait characterized by a predominance of

small, dense LDL and associated with increased CVD risk): 1) there will be a coordinate increase in levels of large HDL particles that are considered anti-atherogenic and large LDL particles that are not associated with increased CVD risk; 2) this change in lipoprotein profile will result in a higher proportion of pattern B individuals converting to LDL subclass pattern A (predominance of larger LDL); and 3) the coordinate increase in large HDL and LDL is due to a common underlying pathway. The latter hypothesis will be addressed by assaying cholesterol ester transfer protein (CETP), hepatic lipase (HL), and lipoprotein lipase (LPL).

These hypotheses will be tested by a dietary intervention study in which saturated fat intake will be increased from 8% to 20% total energy (%E) using primarily dairy products. Saturated fat will be exchanged for monounsaturated fat without changes in carbohydrate, protein, and total fat content. Furthermore, the two experimental diets will be designed to contain a difference of approximately 2.5%E of myristic acid (14:0) and 5.5%E of palmitic acid (16:0) as they are considered major cholesterol-raising fatty acids and are relatively abundant in dairy fat.

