### 3. Project Design

#### Overview

The study is designed to test the hypothesis that an increase in dairy-derived saturated fat intake, in the background of a moderately reduced carbohydrate level and independent of body weight, will increase levels of large HDL and large LDL in pattern B individuals. This will be a controlled, randomized parallel-arm 6-week dietary intervention trial in 50 overweight or obese pattern B individuals. It will begin with a 3-week diet run-in period on a diet containing 55% carbohydrate, 15% protein, and 30% fat, with 8% saturated and 12% monounsaturated fat. A 3-week diet period has been shown to be sufficient for the

[figure not shown]

**Figure 3:** Proposed experimental design. After a 3-wk run-in, 50 pattern B subjects are randomized to either a low or high saturated fat diet for 3 wks.

stabilization of lipid and lipoprotein levels [3, 30]. At the end of this diet phase, subjects will be randomized to either a moderate carbohydrate, low saturated fat diet or to a moderate carbohydrate, high saturated fat diet containing the same proportions of carbohydrate (35%), protein (25%), and total fat (40%), and with either 8% or 20% saturated fat and 22% or 10% monounsaturated fat. Defining LDL pattern based on the run-in diet will allow for the subsequent comparison of pattern B to pattern A conversion rates between the high and low saturated fat diets. The expected 20% of subjects that convert to pattern A on the run-in diet will remain in the study. The two experimental diets will be designed to differ in myristic acid content by approximately 2.5% total energy and palmitic acid of approximately 5.5% (see power calculations). Based on our previous studies, these differences should be sufficient to result in selective increases in levels of large LDL particles. Dietary content of cholesterol and fiber will be similar in the two diets. Subjects will remain weight stable throughout the study. At the end of each diet phase, subjects will undergo a fasting blood draw on two consecutive days. A summary of the experimental design is shown in **Figure 3**.

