## Clinical Procedures

**Clinical measurements:** Blood pressure will be measured 3 times in a sitting position and the last 2 values averaged. Anthropometric measurements include height, weight, waist and hip circumference, and % body fat by bioimpedance (Tanita scale). In our previous study ([name], unpublished), we showed that the major results using this measurement did not differ significantly from those by DXA. Waist circumference is measured two times at the iliac crest and hip circumference is measured at the widest point of the hips.

**Blood sampling:** Using standard blood collection procedures, blood samples will be collected from participants after a 12-14 hour fast. The blood will be collected into tubes containing the following preservative solution: 3.0 gms EDTA (dipotassium), 1.7 mg P-Pack, 0.15 gms gentamycin sulfate, 0.15 gms chloramphenicol, 5.96 mls aprotinin (Sigma A-6279), and 0.30 gms sodium azide all of which are diluted to 20mls with

doubly deionized water. Plasma is separated by immediate centrifugation at 4°C. Lipid and lipoprotein measurements are performed as described below and aliquots of plasma are frozen for future analyses (8, 1ml each). Post-heparin plasma samples will be collected after a heparin bolus for lipase activity assays.

Plasma analyses: At the screening visit (V1), plasma will be analyzed for total cholesterol, LDL-cholesterol, HDL-cholesterol, triglycerides, glucose, TSH, and LDL peak particle size for LDL phenotype determination. At V2a and V3a (first visits before and after randomized diet), measurements will include total cholesterol, LDL-cholesterol, HDL-cholesterol, triglycerides, apolipoprotein A1 and B, LDL phenotyping, lipoprotein subfraction analysis by ion mobility, CETP activity, and post-heparin HL and LPL activity. We will also collect white blood cells and buffy coats for future genetic analyses. A portion of the white blood cells will be immortalized to generate permanent cell lines. At visits V2b and V3b (second visits before and after randomized diet), measurements will include total cholesterol, LDL-cholesterol, HDL-cholesterol, triglycerides, and lipoprotein subfraction analysis by ion mobility. The blood-drawing schedule is shown in **Figure 5**.

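### LDL pattern conversion: phenotyping is listed only at the first draw of each pair and the test is an unadjusted chi-square, so second-draw and run-in diameters already being collected may go unused

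*Protocol*

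**What the plan says.** Hypothesis 2 (Protocol, section 2) is that "this change in lipoprotein profile will result in a higher proportion of pattern B individuals converting to LDL subclass pattern A". The Overview in section 3 sets the reference point: "Defining LDL pattern based on the run-in diet will allow for the subsequent comparison of pattern B to pattern A conversion rates". It adds: "The expected 20% of subjects that convert to pattern A on the run-in diet will remain in the study". The test is fixed in Data Analysis: "Comparison of LDL pattern conversion rate between high and low saturated fat diets will be analyzed by Chi-squared analysis".

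Under Plasma analyses in Clinical Procedures, the V2a and V3a list includes "apolipoprotein A1 and B, LDL phenotyping, lipoprotein subfraction analysis by ion mobility, CETP activity". The V2b and V3b list has the lipids and ion mobility subfractions but does not name phenotyping. Laboratory procedures says that ion mobility gives LDL peak particle size, the quantity that defines pattern B (below 208.8 Å). Data Analysis says, without naming endpoints, that values from the two draws will be averaged.

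On expected size, the protocol says "we expect that 48% pattern B participants will convert to pattern A" for the 12% saturated fat difference, and gives 71% for the myristic acid difference. It gives no rate for the low saturated fat arm and no power for conversion. The stated power concerns continuous endpoints: "With 25 subjects/group, we have adequate power (80%) to detect the expected changes in LDL I, LDL diameter, and HDL2b".

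**The concern.** Conversion depends on whether a noisy diameter falls on one side of a cut-off at two time points. If each classification uses one draw, day-to-day variation near 208.8 Å misplaces people twice: in the set able to convert at V2, and in the outcome at V3. Noise conversions occur in both arms and dilute the contrast. The chi-square also ignores how far below the cut-off each person started, which largely determines who can cross it.

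Only about 20 of 25 completers per arm are expected to be able to convert, so lost precision matters. The second-draw diameters and the run-in diameter are already being collected. What is at stake is the precision of one of the trial's three named hypotheses.

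**Working it through.** **1. The plan's own figures.** Inputs from Data Analysis: 25 per group, 80% power, and 5% significance ("estimated at 80% statistical power, 5% significance", given for Table 2; two-sided reproduces the tables). Detectable difference = (1.960 + 0.842) × (SD/√2) × √(2/25).
- LDL-I: 2.802 × (29.6/√2) × 0.2828 = 16.59 mg/dl (stated 16.6).
- LDL diameter: 2.802 × (5.0/√2) × 0.2828 = 2.80 Å (stated 2.9; 2.86 with the t distribution).

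The tables therefore assume that averaging two draws halves the variance of change. This is exact only if all of that variance is day-to-day: 5.0² = 2d² gives a daily SD of d = 3.54 Å.

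**2. Participants able to convert.** 25 × (1 − 0.20) = 20 per arm, if run-in converters split evenly.

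**3. Power of the planned chi-square.** Exact enumeration of two binomials, 20 per arm, uncorrected Pearson test, two-sided 5%. The low-saturated-fat-arm rate is an assumption, because the protocol gives none.

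| Low-arm rate | High arm 48% | High arm 71% |
|---|---|---|
| 5% | 93% | >99% |
| 10% | 80% | 99% |
| 15% | 65% | 97% |
| 20% | 48% | 92% |
| 30% | 21% | 74% |
| 40% | 7% | 49% |

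Power of 80% holds up to a low-arm rate of about 10% (high arm 48%) or 27% (high arm 71%).

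**4. What averaging and adjustment gain.** This needs a simulation. Table 1 supplies the SD of change (5.0 Å, taken as single-draw) and the effect (4.9 Å). The rest is assumed: true V2 diameter normal with mean 205.5 and SD 3.5 Å, daily SD 1.5 to 3.5 Å, and no mean shift in the low arm. Response SD = √(25 − 2d²), which is 4.53 Å at d = 1.5 and 0.71 Å at d = 3.5. About 19 to 20 per arm are then classified pattern B at V2.

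| Conversion test | Power, d = 1.5 to 3.5 Å | Repeat run, 4,000 trials per setting |
|---|---|---|
| Single draw, chi-square | about 57-70% | 58-68% |
| Two-draw mean, chi-square | about 60-86% | 63-84% |
| Two-draw mean, logistic adjusted for V2 diameter | about 67-93% | 68-90% |

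In the repeat run the simulated two-draw conversion rates were 13-21% (low arm) and 54-56% (high arm). These are therefore not powers at 48%.

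**5. Check on the adjusted test.** With about 40 people in the model, the ordinary likelihood-ratio test rejected in about 5-10% of trials with no diet effect, so part of its advantage is not real. Two safer versions were run on two-draw means at d = 1.5 and 3.5 (1,500 trials each):
- Firth-penalised logistic regression: power 63-88%, false-positive rate 3-5%.
- Adjusted risk difference with robust standard errors: power 61-87%, false-positive rate 4-5%.

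Most of the dependable gain comes from averaging. Adjustment adds at most a few points.

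**6. The continuous companion.** A two-sample t-test on change in diameter, 4.9 Å with 25 per arm, has 92% power at SD 5.0 and over 99% at 5.0/√2.

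**The case against.** The strongest reply is that nothing here is invalid. An unadjusted chi-square is a sound test in a randomized comparison. Conversion is not among the Table 1 primary endpoints, and no power is claimed for it. The general averaging sentence may already cover phenotyping, and a statistical analysis plan, not shown, may settle the rule. All of this stands, and it makes the point one of efficiency and clarity.

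The size of the gain is also open to challenge. At a daily SD of 1.5 Å, averaging adds only about 3 or 4 points. At 3.5 Å the gain is large, but almost no individual variation in response is left. That also stands, although the larger value is close to what the protocol's own halving of variance implies (step 1).

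A reader might infer three stronger things that the documents do not support:
- **That the test cannot succeed at 48%.** Power there runs from 93% to 7% over low-arm rates of 5% to 40%. That arm also moves from 55% to 35% carbohydrate, which the Background says lowers small, dense LDL, so an appreciable rate is plausible. The protocol gives no figure.
- **That single-draw phenotyping is fixed.** It is an inference from the visit list, and the averaging sentence points the other way.
- **That the continuous measurement is thrown away.** LDL diameter is a Table 1 primary endpoint tested by analysis of variance. It does not itself test a hypothesis about the proportion converting, but it should be read with it.

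**Conclusion.** The point holds as a missed efficiency together with an ambiguity about which draws define the pattern. Two-draw classification with adjustment for run-in diameter raises power for conversion from about 57-70% to about 67-93% with ordinary logistic regression, or to about 61-88% with the safer versions in step 5. The gain is modest if day-to-day variation is small and large if it is near the value implied by the protocol's tables.

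These figures rest on normal diameters, the assumed V2 mean and SD, a 4.9 Å effect, a single-draw reading of the 5.0 Å SD, 25 completers per arm and no mean shift in the low arm. They support the choice of analysis, not a finding that the planned test is inadequate. Adequacy cannot be judged without a low-saturated-fat-arm rate.

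**What to change.** - Define pattern at V2 and V3 from the mean LDL peak diameter of both draws (V2a with V2b, V3a with V3b), and state this in Data Analysis so that the visit list and the averaging sentence agree.
- Count conversion among participants who are pattern B on the V2 mean, expected to be about 20 per arm.
- Replace the unadjusted chi-square with logistic regression adjusted for V2 mean diameter, preferably penalised at this sample size, or an adjusted risk difference with a confidence interval.
- Report the result alongside the planned continuous LDL diameter analysis.
- If an expected conversion rate is kept, giving the assumed low-saturated-fat-arm rate beside it would let readers judge power. This is a clarification only.

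The cost is analysis wording, best fixed before outcome data are seen. No visit, assay or participant is added, because ion mobility is already run at all four draws.

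### The detectable differences in Tables 1 and 2 halve the whole variance of change for averaging two draws, a best case that is unavailable for apo AI and apo B and leaves HDL2b power at the 12% saturated fat contrast at 66–92%

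*Protocol*

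**What the plan says.** The Data Analysis section plans a one-way analysis of variance on mean change between two diets, with 25 subjects per group. It states: "With 25 subjects/group, we have adequate power (80%) to detect the expected changes in LDL I, LDL diameter, and HDL2b", and says that this holds for either the 12% saturated fat contrast or the 2.5% myristic acid contrast. It adds that "we will use the average value of measurements from two blood draws on consecutive days to reduce variance and increase power".

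Table 1 gives, for each primary endpoint, an SD of difference and a detectable difference, for example "HDL2b (mg/dl) | 11.5 | 6.5" and "LDL-I (mg/dl) | 29.6 | 16.6". Table 2 does the same for nine other endpoints, "estimated at 80% statistical power, 5% significance using baseline concentrations and standard deviation of response observed in our previous controlled dietary trials". Both tables carry the footnote "Detectable differences assume the average of 2 baseline and 2 post-diet measurements".

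Under Clinic Visits, the two draws at each time point are 24–96 hours apart. Under Clinical Procedures (Plasma analyses), lipids and ion mobility are measured at both draws. Apolipoproteins A1 and B are listed only at V2a and V3a.

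**The concern.** A second draw a day or so later averages out assay error and day-to-day fluctuation. It does not average out real differences between participants in how they respond to the diet, because both post-diet draws carry the same response. If the whole variance of change has been divided by two, the detectable differences are too small for the power attached to them unless participants respond identically and the errors on the two days are independent.

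At stake are the detectable differences printed in both tables and, among the primary endpoints, the power statement for HDL2b. Large HDL is one half of the first hypothesis, and HDL2b has the smallest margin between detectable and expected difference in Table 1 (6.5 against 7.9 mg/dl).

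**Working it through.** **Inputs.** 25 per group, 80% power, the SDs of difference and the detectable and expected differences are from Data Analysis and Tables 1–2. The 5% level is stated for Table 2 and assumed for Table 1. Sidedness is not stated; two-sided is assumed because it reproduces the tables.

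**Step 1: reproduce the printed figures.** The two-sample detectable difference is (1.960 + 0.842) × SD × √(2/25) = 0.792 × SD, or 0.809 × SD with the noncentral t. Dividing by √2 gives 0.560 (normal) or 0.572 (t).

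| Endpoint | SD | Stated | Ratio | Full SD (normal–t) |
|---|---|---|---|---|
| HDL2b | 11.5 | 6.5 | 0.565 | 9.1–9.3 |
| LDL-I | 29.6 | 16.6 | 0.561 | 23.5–23.9 |
| LDL diameter (Å) | 5.0 | 2.9 | 0.580 | 4.0 |
| Triglycerides | 117.97 | 65.98 | 0.559 | 93.5–95.4 |
| Total cholesterol | 25.97 | 14.52 | 0.559 | 20.6–21.0 |
| LDL-C | 24.60 | 13.76 | 0.559 | 19.5–19.9 |
| HDL-C | 5.34 | 3.05 | 0.571 | 4.2–4.3 |
| Apo AI | 9.49 | 5.31 | 0.560 | 7.5–7.7 |
| Apo B | 25.50 | 14.26 | 0.559 | 20.2–20.6 |
| LDL-2 | 35.00 | 19.58 | 0.559 | 27.7–28.3 |
| LDL-3 | 25.02 | 13.99 | 0.559 | 19.8–20.2 |
| LDL-4 | 15.71 | 8.78 | 0.559 | 12.4–12.7 |

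Units are mg/dl except diameter. All 12 rows match SD/√2 within rounding. With the full SD, a one-sided test (0.703) or 32 per arm (0.700) does not match. A one-sample formula with n = 25, or 50 per arm, also gives 0.560, but neither fits a two-group design with 25 per group. The footnote on averaging is the natural explanation.

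**Step 2: what averaging can do.** Write the single-draw variance of change as R + 2D, where R is between-person response variance and D is the day-to-day plus assay variance of one draw. With two draws averaged at each time point and independent errors, it becomes R + D. If r = R/(R + 2D) is the response share, the remaining fraction is r + (1 − r)/2 = (1 + r)/2. This is 0.5 only when r = 0. The protocol gives neither R, nor D, nor a correlation between draws.

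**Step 3: power at the tabulated differences (noncentral t, 25 per arm).** With full halving (r = 0) it is 78–81% across the rows. With no reduction it is 49–52% (51–54% by the normal formula).

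**Step 4: power at the expected differences of Table 1 (noncentral t).**

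| Endpoint and contrast | Expected | No reduction | Full halving |
|---|---|---|---|
| HDL2b, 12% saturated fat | 7.9 | 66% | 92% |
| HDL2b, 2.5% myristic | 10.7 | 90% | >99% |
| LDL-I, 12% saturated fat | 39.2 | >99% | >99% |
| LDL-I, 2.5% myristic | 49.6 | >99% | >99% |
| LDL diameter, 12% saturated fat | 4.9 | 92% | >99% |
| LDL diameter, 2.5% myristic | 6.1 | 99% | >99% |

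For HDL2b at 7.9, power is 80% when the remaining variance fraction is (7.9 / (0.809 × 11.5))² = 0.722. Then r = 2 × 0.722 − 1 = 0.44. Above a response share of about 44%, power is below 80%. The normal formula puts the threshold at about 50%.

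**Step 5: apo AI and apo B.** Only one draw per time point is listed for these assays, so no averaging applies whatever r is. The full-SD values in the first table are the ones that match the plan.

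**The case against.** The strongest reply is that the sentence claiming 80% power concerns the expected changes, not the detectable ones, and largely survives. Five of the six endpoint-by-contrast cells stay at about 90% or more with no variance reduction at all. Large LDL, the comparison that Data Analysis names as testing the hypothesis, is above 99%. This stands. A reader might infer from the tables that the sample size rests on the halved variance, or that the trial as a whole is underpowered; the protocol's own expected differences do not support either.

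A reader might also infer that HDL2b power at the 12% contrast is below 80%, or that power at the tabulated differences is about 50%. Neither is shown. Both are the unfavourable end of a range, and the protocol has no figure that places the truth within it. The Background remark that genes and diet influence the expression of pattern B does not establish how much people differ in their response to saturated fat. Zero difference is a strong assumption, but the actual size is unknown.

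It is also uncertain what the SDs contain. The ion mobility SDs quoted in Data Analysis, 20.9 mg/dl and 3.5 Å, equal 29.6/√2 and 5.0/√2 to the printed precision. If the Table 1 SDs are √2 times a purely within-person SD, averaging would halve their variance, but response variance would then be missing from them and the full-SD figures would not be upper bounds. If the SDs already come from averaged draws, no further reduction is due. The protocol does not say which applies.

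Finally, the averaging assumption is openly footnoted, and Table 2 states no expected differences. That limits the consequence but does not make the printed figures right.

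**Conclusion.** The concern holds in limited form. The detectable differences in both tables assume that averaging two draws halves the whole variance of change. That is a best case, needing no between-person variation in response and independent errors on the two days, and the protocol supports neither condition. Taking the SDs as single-draw SDs of change, power at the tabulated differences is somewhere between about 49–52% and about 80%.

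Two rows conflict with the measurement schedule without any assumption about response: apo AI and apo B are understated by a factor of about √2.

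Of the power claims for the expected changes, only HDL2b at 7.9 mg/dl is in doubt. It holds if response makes up less than about 44% of the single-draw variance of change, and fails otherwise. These figures assume a two-sided 5% test with 25 completers per arm.

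**What to change.** 1. State whether the SDs of difference come from single or averaged draws.
2. Recompute Tables 1 and 2 with response variance plus day variance, estimating the split from replicate draws in earlier in-house diet studies. If there are no replicates, print the detectable difference as a range from SD/√2 to the full SD, for example HDL2b 6.4–9.1 and LDL-I 16.6–23.5 mg/dl (normal formula).
3. Use the full SD for apo AI and apo B, or reconcile Table 2 with the list of assays at V2b and V3b.
4. Restate power for HDL2b at the 12% saturated fat contrast as the resulting figure, or as 66–92% if the split is unknown. The claims for the other five cells can stay.

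The cost is a recalculation and less favourable printed figures. No additional participants and no change to endpoints or analysis follow from this point.
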